## Discussion

Emotions guide our decisions, facilitate responses to the environment and constitute the foundation of social interaction. Emotions that are appropriately expressed in their context in terms of timing and intensity are more likely to facilitate adaptive responses. Therefore, it is vital for people to be able to regulate their emotional response, in order to favor social interaction and maintain mental health. Some psychological disorders, such as ASD, IED, among many others, are characterized by emotional dysregulation. Consequently, people who suffer from them may show aggressive behavior, irritability, and anxiety.

In this context, interoception emerges as a key component in emotional self-regulating mechanisms involved in acting out [55]. Several reports have proven that a low interoception accuracy is associated with a lower emotional awareness, higher reactivity and difficulties in modulating responses under stress or frustration [56]. As the brain fails in identifying body sensations linked to emotional states (e.g: heart rate, muscular distress, etc.), a crucial information source to anticipate and regulate intense emotional responses is lost. This disconnection between body and mind may allow the appearance of acting out, due to a fail in emotional processing.

Of course, aggressive outbursts do not only appear in IED, ADHD, or ASD, as there are many personal circumstances, experiences, or psychological disorders that make people manifest aggressive episodes. We find cases in people who have suffered from a history of childhood abuse, alcohol use disorder (AUD) [57], military veterans PTSD [58], borderline personality disorder (BPD) [59], etc.

Dysfunction in the amygdala-OFC cortex network produces emotional dysregulation. Individuals with IED show irregularities within this network, with increased activity in the amygdala, a hypoactivated OFC, and reduced coupling between those areas compared to healthy people in response to social threat signals [60]. As the amygdala is important for processing emotions, and the OFC is implicated in decision-making and processing of reward/punishment, this activity pattern suggests that these people are vulnerable to intense negative emotions, have a deficit in their ability to regulate and control them, and are prone to impulsivity [61] in IED. Similarly, patients with BPD show reduced lateral prefrontal activity during emotional action control compared to healthy volunteers. Furthermore, anger has been negatively related to prefrontal activity, while it has been positively related to amygdala activity. Therefore, deficits in lateral prefrontal cortex seem to be a common neural mechanism underlying anger-related aggression for this population [59]. This prefrontal cortex dysfunction may stem from incorrect signaling between different neural hubs. In fact, neurobiological research has demonstrated that impulsive aggression is caused by serotonin dysregulation in receptor-specific pathways in the prefrontal cortex [62].

Although emotions originate in the brain [63], their expression affects the entire human body. As explained above, physiological arousal is manifested by an increase/decrease in the activity of several organs innervated by the branches of the peripheral nervous system. For example, HR can be accelerated/de-accelerated by an increase in the activity of the SNS or PNS, respectively. Additionally, an increase in SNS activity facilitates the production of sweat in the skin [64], or hormones, such as cortisol, which increases blood pressure. This cascade of physiological responses as a consequence of an emotion can be measured by devices that show the body’s reaction to people who have difficulty interpreting their emotions. This study suggests the use of primarily HR, HRV and SCL measures for biofeedback purposes, as a way of interoception enhancement. Biofeedback might enable alternative pathways in the brain to allow interpreting and integrating emotional information, increasing activity and connectivity in the insula, a region associated with internal bodily awareness, and in the ACC and PFC, which are critical for executive functions and impulse control. This improved neural regulation may lead to increased emotional awareness and a greater ability to modulate automatic aggressive responses.

### Study limitations

The application period of biofeedback therapy, along with the time required to recognize the physiological variables used to identify the preparatory state that precedes an aggressive outburst, might be too short to achieve significant results to validate the therapy. Should it be the case that the results do not show changes in the subjects, sessions S6–S9 will be repeated.

If an aggressive impulse involves numerous movements by the individual, the capture of physiological signals, and consequently the extraction of features derived from those signals, could be significantly disrupted, which in turn may affect the detection of the preparatory state.

There may also be an environmental inhibition effect when attempting to provoke an impulsive response in the laboratory. This could be a serious limitation, as it might significantly reduce the amount of valid data available for training artificial intelligence models, thereby diminishing the power of the proposed statistical analysis.

The equipment used to measure physiological signals could be damaged during aggressive responses. Although replacement materials have been planned, they might be insufficient, requiring additional budget and time to conduct the tests.

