## Materials and methods

### Participants

As explained above, the early onset of aggressive behavior is linked to higher biological risks and often leads to persistent antisocial behavior, highlighting the importance of applying treatment at early age. For this reason, the group to be studied will consist of 70 participants aged 10–16 years. They will be recruited from the INEBIR clinic, where the experimental sessions will be carried out, and other participants will be recruited from the Instituto Hispalense de Pediatría. The sample size was by analyzing the differences of the means according to a Student’s t with a confidence level of α=0.05, a test power of 1−β = 0.8 and a moderate effect size [30]. A moderate effect size (Cohen’s d = 0.5) represents a practically meaningful difference in the context of clinical decision-making, even if smaller effects may also be statistically detectable in larger samples and it is a commonly used convention in behavioral and clinical research when planning exploratory studies [31]. A moderate effect size results in 62 participants. For a small effect size (Cohen’s d = 0.2), we would need to recruit more than 300 participants, and we do not have the human and material resources to complete this study in a relatively short time. Additionally, to account for potential non-response or dropout, we included an additional 10%, bringing the final target sample size to 70 participants. This approach ensures sufficient power to detect differences between groups while anticipating common challenges in recruitment and retention.

To participate in this study, the following inclusion criteria will be applied:

Adolescents aged 10 to 16 whose parents seek professional help because their son or daughter exhibits aggressive outbursts that they are unable to manage.Intermittent aggressive episodes with a frequency of at least once a week in the two months prior to the start of the intervention.Not presenting some of the following:History of bipolar or psychotic disorder.Head trauma with loss of consciousness for more than 60 minutes.

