**Block 3.**

S5 Only for the intervention group. The adolescents will be trained to identify the physiological response when they are relaxed and when an outburst is coming. It is possible to use these responses to predict the aggressive outburst at least one minute before it manifests [42]. To do this end, the VR system receives and shows HR, HRV, and SCL on the virtual scenario. Therapists will help participants identify the physiological features related to aggressive outburst based on the data collected in previous sessions (Block 2).S6–S9 They are similar in both intervention and control groups, and follow the same layout as the sessions in block 2, excluding the last phase:**Cognitive therapy in the control group.** After evoking an outburst, adolescents will be trained with cognitive, behavioral and emotional self-regulation therapies [43], which have proven their effectiveness for managing anger and learning positive coping skills. The underlying theory is that people can minimize their negative feelings and behaviors when they are aware of their irrational beliefs and work to change their minds, by focusing on them continuously. With this therapy, people are endowed with strategies to improve their capabilities of identifying negative thoughts and beliefs in situations of conflict and/or frustration, which are the main triggers of aggressive outbursts. The goal is to ensure that, through identifying such thoughts and becoming more aware of their emotions, the individual gradually dismantles those irrational thoughts.**Cognitive therapy in the intervention group.** Participants will follow the same cognitive therapy as the controls, although they will receive information through biofeedback. By identifying this information and applying the skills learned in therapy, participants are expected to better manage or avoid imminent outbursts.

At the end of session S9, the CACIA, Stroop, CBCL, YSR and WCST tests will be assessed again. The differences between the new obtained physcological scores, with respect to the initial scores, along with the differences between control and intervention groups, will be used to assess the efficacy of the intervention.

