#### Assessment of cognitive therapy with biofeedback.

The main goal of this study is to verify the efficacy of the proposed therapy. At the beginning adolescents will fill in the CACIA, Stroop, WCST and CBCL tests. At the end of the therapy, these metrics will be assessed once more to compute the difference with the initial tests. These differences will be compared between the intervention and control groups to ascertain statistical significance. To this end, we will use the Mann-Whitney-Wilcoxon test, or the one-way ANOVA, depending on the distribution of residuals, to determine whether samples originate from the same distribution

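### Repeating S6–S9 when the results show no change makes the efficacy endpoint time depend on the data and, on one plausible reading, allows a second unadjusted test

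*Protocol article*

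**What the plan says.** Three places in the protocol article bear on when efficacy is measured.

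- Block 3 ties the post-test to a session: "At the end of session S9, the CACIA, Stroop, CBCL, YSR and WCST tests will be assessed again". The change from the initial scores, and its difference between arms, is to be the measure of efficacy.
- The analysis section on cognitive therapy with biofeedback places it at the end of treatment: "At the end of the therapy, these metrics will be assessed once more to compute the difference with the initial tests". The change scores are then compared between arms for significance, by Mann-Whitney-Wilcoxon or one-way ANOVA. One comparison is described.
- Study limitations first notes that the treatment period may be too short for a significant result, then adds a conditional rule: "Should it be the case that the results do not show changes in the subjects", S6–S9 will be run again.

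Participants sets "a confidence level of α=0.05" for the sample size. No section divides that level between two analyses.

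**The concern.** The repeat is worded as a commitment, and it can only be triggered by looking at results. It works in one direction: a favourable first look ends treatment at S9, and an unfavourable one extends it. S6–S9 are four sessions, so a repeat takes the therapy sessions from four to eight. At the stated pace of one session a week, it also moves the last assessment by about four weeks.

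Two things are at stake. First, the endpoint has no single definition: the end of therapy means the first S9 or a repeated S9, depending on what was seen. Second, if the first between-arm test counts when it succeeds and a second one counts when the first fails, the efficacy claim gets two chances at the full 0.05.

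A further problem arises only if the repeat is decided participant by participant. The amount of treatment before the final test would then depend on response and could differ between arms.

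**Working it through.** **Inputs from the article.** Alpha 0.05 (Participants), taken as two-sided because no side is stated; this is an assumption. Equal allocation (Participants). One planned between-arm comparison of change scores (analysis section). Repeat rule as in Study limitations.

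**Input not in the article.** The correlation ρ between the between-arm test statistics at the first and second assessments. The same participants and the same initial scores enter both, so it should be positive. I show 0 to 0.95.

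**Step 1: the plan without the repeat.** One test at two-sided 0.05 has a false-positive rate of 5.0%. Simulated t-tests with 31 per arm gave 4.8% to 5.0%.

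**Step 2: the trigger is a non-significant between-arm result, and significance at either time counts.** The second test is done only when the first fails, so

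P(false positive) = P(reject first) + P(not reject first, reject second) = 1 − P(|Z₁| ≤ 1.96 and |Z₂| ≤ 1.96),

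with (Z₁, Z₂) bivariate normal with correlation ρ. At ρ = 0 this is 1 − 0.95² = 0.0975. The last column is the level per test that would bring the total back to 5%.

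| ρ (assumed) | False-positive rate, each test at 0.05 | Level per test for 5% overall |
|---|---|---|
| 0 | 9.75% | 0.025 |
| 0.3 | 9.5% | 0.026 |
| 0.5 | 9.1% | 0.027 |
| 0.7 | 8.3% | 0.029 |
| 0.8 | 7.8% | 0.031 |
| 0.9 | 7.0% | 0.035 |
| 0.95 | 6.5% | 0.038 |

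Simulated t-tests with 31 per arm agree: 8.8%, 8.3% and 7.1% for ρ = 0.5, 0.7 and 0.9. More than one repeat, which the text does not rule out, would raise the rate further.

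**Step 3: the trigger is no pooled within-subject change.** I simulated 31 per arm with no difference between arms, a common change of 0 or 0.25 SD, ρ from 0.5 to 0.9, and a repeat when a one-sample test of the pooled change is not significant at 0.05.

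- Only the last assessment counts: 4.8% to 5.1%.
- Significance at either assessment counts: 6.2% to 9.0%.

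**Step 4: how often a between-arm trigger would fire.** The article plans for "a test power of 1−β = 0.8" at d = 0.5 and states: "A moderate effect size results in 62 participants". With 31 per arm, the noncentrality is 0.5 × √(31/2) = 1.97 on 60 degrees of freedom, and two-sided power is 49% (54% with 35 per arm). So even if the assumed effect is real, a non-significant first result is about as likely as not. The stated 62 does not reproduce as a total: the two-sided requirement is 63 per arm by the normal formula or 64 by exact t. That is a separate matter, and steps 2 and 3 do not depend on it.

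**The case against.** The strongest case on the other side has four parts.

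1. *The rule speaks of changes in the subjects, not of a difference between arms.* It can be read as pooled within-subject change, with the last assessment as the only one that counts. Step 3 then gives about 5%. This stands as a possible reading, so a reader who infers that the false-positive rate necessarily exceeds 5% goes beyond the text. But the article does not state that reading either, and the sentence just before the rule links the repeat to a failure to reach significance.

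2. *No second assessment or test after a repeat is described, and only Block 3 names S9.* Both are true, and the second test is an inference. But repeating the sessions because results fell short has little purpose for validating the therapy unless participants are assessed again. The analysis section's reference to the end of therapy would then point to a later date than Block 3 does.

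3. *A reader might infer that the estimate will mix two treatment durations selected on outcome.* The article does not support that as it stands. Both arms attend S6–S9, and a repeat decided for the whole trial would give everyone the same extension. Mixing follows only if repeats are decided individually, which the text neither says nor excludes.

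4. *A reader might extend the inflation to every variable on the primary list.* That list has nine entries: six psychometric (two CACIA scales, and two T-scores each from CBCL and YSR) and three physiological. The between-arm efficacy test covers psychological scores. The physiological signals are compared before versus during an outburst and home versus laboratory. Any total over several outcomes would also be mostly ordinary multiplicity, which is a different issue.

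The rule is one sentence under Study limitations and does not appear in the Analysis section. That placement does not make it harmless, because it commits the study to an action. It is a rule the article states, not a detail left to an analysis plan.

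**Conclusion.** The point holds in two parts of different strength.

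- **Endpoint time.** On any reading, the point at which therapy ends depends on the observed results, and the article does not say which assessment is then the efficacy endpoint. Block 3, the analysis section and Study limitations must be reconciled. This needs no assumption about the trigger.
- **False-positive rate.** For one outcome it can rise from 5% to about 7.0% to 9.5%. This requires that the trigger is a non-significant between-arm result, that significance at either assessment counts, that each test uses two-sided 0.05, that there is one repeat, and that ρ lies between 0.9 and 0.3. With the other conditions met, the rate is above 5% for every ρ below 1. It stays near 5% if the trigger is pooled within-subject change and only the last assessment counts.

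Exposure that depends on response is a third risk, conditional on participant-level repeats. The matter has to be settled before any results are seen, because the choice of endpoint could not be defended afterwards.

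**What to change.** State that the efficacy analysis is the first post-S9 assessment of all randomised participants, and that it is reported whatever it shows. State that data collected after any repeated sessions are exploratory and neither replace the S9 result nor are pooled with it.

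If a later assessment is to count for efficacy, plan it for everyone in both arms and split alpha in advance. A level of 0.025 at each of two assessments holds 5% at any correlation, since 0.025 + 0.025 = 0.05. A larger level relies on an assumed correlation: 0.029 per look is right for ρ of about 0.7, but gives 5.4% at 0.5 and 5.6% at 0.3.

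The cost is one or two sentences in the protocol and the loss of a second confirmatory test at the full 0.05. Whether sessions are repeated as care is a clinical decision on which no position is taken here.

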## Conclusion

By using biofeedback with cognitive, behavioral and emotional self-regulation therapies, we aim to improve the social skills of people with emotional dysregulation and reduce the frequency of aggressive episodes. This randomized control trial seeks to evaluate the effectiveness of including biofeedback in the therapy.

Although we will use HR, HRV and SCL for biofeedback purposes, a wider set of physiological features will also be studied. The goal is to pinpoint a small and significant set of features that are the best predictors for an incoming outburst.

This reduced set of features could allow designers to develop a minimal piece of equipment. The signals in the ensuing set could then be merged into a unique warning signal before the outburst so that people can apply the learned self-regulation mechanisms, and avoid or minimize the aggressive episodes.
